**Inclusion criteria / exclusion criteria EXPLORATIVE STUDY**

**Inclusion criteria:**

- - 1. Signed informed consent form.
    2. Male gender to avoid the gender-related differences in ethanol metabolism38.
    3. Between 18-45 years to avoid age-related changes in ethanol metabolism39.
    4. Normal medical history and physical examination.
    5. Normal liver function tests (i.e. ALT, AST, and γGT) according to the reference values for normal ranges of the liver enzymes at the laboratory of clinical chemistry of Maastricht University Medical Center.
    6. Caucasian ethnicity.
    7. BMI=18 – 30 kg/m2.

**Exclusion criteria:**

1. History of gastro-intestinal disorders or abdominal surgery.
2. History of alcohol abuse or current excessive alcohol consumption (> 2 alcoholic beverages per day or > 14 alcoholic beverages per week)40.
3. Recent or chronic medications that may interact with ethanol metabolism or intestinal permeability i.e., NSAIDs, benzodiazepines and antidepressants.
4. Smoking.

**General considerations:**

- Diet:
  - Continuation of regular dietary habits.
  - Standardized meals three days prior to each study day.
- Dose of ethanol :
  - 20 grams of ethanol. This will be the starting dose, which will be increased gradually (i.e 30 g maximum) if necessary. (See also the explorative study).

**Inclusion criteria / exclusion criteria DEFENTITIVE STUDY:**

**Inclusion criteria:**

1. Signed informed consent form.
2. Male gender to avoid the gender -related differences in ethanol metabolism38.
3. Between 18 - 45 years to avoid age-related changes in ethanol metabolism39.
4. Normal medical history and physical examination.
5. Normal liver function tests (i.e. ALT, AST, and γGT) according to the reference values for normal ranges of the liver enzymes at the laboratory of clinical chemistry of Maastricht University Medical Center.
6. Caucasian ethnicity.
7. BMI=18 – 30 kg/m2.

**Exclusion criteria:**

1. History of gastro-intestinal disorders or abdominal surgery.
2. History of alcohol abuse or current excessive alcohol consumption (> 2 alcoholic beverages per day or > 14 alcoholic beverages per week)40.
3. Recent or chronic medications that may interact with ethanol metabolism or intestinal permeability i.e., NSAIDs, benzodiazepines and antidepressants.
4. Smoking.

**General considerations:**

- Diet:
  - Continuation of regular dietary habits.
  - Standardized meals three days prior to each test day
- Dose of alcohol administration chosen:
- Will be based on the results from the explorative study

**Materials and methods**

**Study design**

**The explorative study**

Five male healthy volunteers will be included in the explorative study. Ethanol 20g will be administered as starting dose, using an intraduodenal catheter. The dose will be increased gradually (i.e 30 g maximum) if necessary. Permeability tests will be performed by a multi- sugar tests. (MEC 08-2-070, MEC 04-168).

[figure not shown]

**Figure 3: Schematic diagram showing the design of the explorative study.**

Healthy subjects selected for the explorative study will be instructed to fast overnight from 22:00 PM and will be requested to arrive at the hospital endoscopy unit at 08.00 AM for blood sampling and insertion of the intraduodenal tube. The correct position of the tube will be checked by an X-ray. Once the tube is situated in the duodenum, 20 g of food grade ethanol (EtOH) diluted in tap water to 200 ml (i.e. final concentration of 10 %) will be infused within 15 minutes. Blood samples will be collected at t = -15 min, t = 15 min, t = 30 min, t = 45 min, t = 60 min, t = 120 min and t = 180 min (See figure 3). At t = 15 min, the sugar solution (5 g lactulose and 0.5 g L-rhamnose in 100 ml of tap water) will be ingested orally. Subjects will be requested to remain fasting and only water and tea without sugar will be allowed until the end of the study day. Urine samples will be collected during the first 5 hours.

The time of biopsy sampling for the definitive study will be determined by the peak of blood ethanol concentration.

**The definitive study**

The definitive study will be executed according to a double-blind, placebo-controlled randomized, crossover trial.

The subjects will undergo two study days in a random order, namely ethanol intervention with permeability tests or placebo intervention with permeability tests, with a one week wash out period in between.

**
[figure not shown]
**

**Figure 4: Schematic diagram showing the design of the definitive study.**

Healthy subjects participating in the study will be instructed to fast overnight from 22:00 PM and will be requested to arrive at 8.00 AM at the hospital endoscopy unit for blood sampling and insertion of the intraduodenal tube. The correct position of the tube will be checked by an X-ray. Once the tube is situated in the duodenum, ethanol (dose will be determined from the explorative study) or the placebo (200 ml of tap water) will be infused within 15 minutes. Blood samples will be collected at t = -15 min, t= 15 min, t= 30 min, t= 45 min, t= 60 min, t= 120 min and t= 180 min (See figure 4).

At t= 15 min, the sugar solution (5 g lactulose and 0.5 g L-rhamnose in 100 ml of tap water) will be ingested orally. Subjects will be requested to remain fasting and only water and tea without sugar will be allowed until the end of the study day. Gastroscopy for biopsy sampling will be performed at t= 60 min (will be modified according to the peak of blood ethanol concentration in the explorative study). Urine samples will be collected during the first 5 hours.

**General considerations**

All subjects participating will be requested to refrain from heavy physical exercises. Consumption of alcoholic beverages will be prohibited during one week prior to each study day. In order to standardize food intake among different individuals, three days prior to each day of the study, standard meals will be provided.

The subjects will be fasting overnight from 22:00 h the night before to 08:00 h in the morning each study day. During the study day, subjects will be allowed only to drink water or tea without sugar. Once all tests are performed, a meal will be provided and a hospital bed will be present to rest when necessary. Before the subjects can leave the hospital, ethanol levels will be determined by exhaled breath test. The exhaled breath test will be performed to determine the legal limit of blood alcohol (BAC) concentration 0.05 g/dl (0.05%). Subject will stay at the motility room located at Maastricht University Medical Center (MUMC), under supervision. Transportation home will be provided (taxi).

**Methods**

**Alcohol administration**

Preparations of sugars and ethanol solutions will be performed in a food grade kitchen at Maastricht University ([name]). The sugars solution will be prepared from 5 g lactulose and 0.5 g L-rhamnose in 100 ml of tap water. The ethanol solution will be prepared from pure food grade ethanol diluted in tap water up to 200 ml (final concentration of 10%). The placebo mixture will consist of 200 ml of tap water.

Because the participants will notice the effects of ethanol as well as the investigator, the solution of ethanol will be prepared and the samples will be recoded by an independent person.

**Blood sampling**

Before and after intraduodenal infusion of ethanol or placebo, blood samples will be collected from an antecubital vein. Each time, 4 mL blood will be collected in 2 K2EDTA-tubes to obtain plasma samples, 4 mL will be collected in a SST-tube to obtain serum. The amount of blood will be 84 ml in total. After collection, one K2EDTA tube will be centrifuged at 2600 rpm for 20 min at 20C. The other K2EDTA will be centrifuged at 2500 rpm for 15 min at 4C, the supernatant will be collected and this will be centrifuged again at 4000 rpm for 10 min at 4C.SST tubes will be kept at 0C and immediately centrifuged at 2600 rpm for 15 min at 4C. Serum and plasma will be collected in 1-mL aliquots and stored at -80C until analysis. Whole blood will be analyzed within 4 hrs and ethanol and acetaldehyde concentrations will be measured immediately.

**Measurements in the blood**

The following parameters will be measured in blood samples, using standard laboratory protocols:

Serum

- Lactulose
- L-rhamnose

Plasma:

- - Circulating cytokines (including IL-6, IL-10, IL-12 and TNF-).
  - Liver function tests (ALT, AST and γGT).
  - C-reactive protein (CRP), Myeloperoxidase (MPO).
  - Intestinal-type fatty acid binding protein (I-FABP) as a marker of cellular damage.

**Gut permeability test**

Permeability of the small intestine in humans can be assessed non-invasively by measuring the serum and urine excretion ratio of ingested water-soluble, non-degradable test probes. Such a barrier function test is based on a comparison of intestinal permeation of a larger molecule (*e.g.* Lactulose) with that of a smaller molecule (*e.g.* L- rhamnose). For the gut permeability tests, the subjects will have to ingest a sugar drink (100 mL) containing 5 g Lactulose (Centrafarm Services, Etten- Leur) and 0.5 g L-rhamnose (Danisco Sweeteners, Thomson, Illinois, USA) after overnight fasting and collection of urine during the first five hours. The serum and urine ratio of these test molecules represents two distinct routes of permeation (*i.e.* paracellular and transcellular) and provides an estimation of the small intestinal permeability. All sugar probes used in this test are accepted and validated parameters of integrity of the intestinal barrier, and provide an accurate estimation of mucosal damage. Serum will be separated from the blood samples within 30 minutes and stored at -80C until analysis. Lactulose and L-rhamnose in serum will be determined by fluorescent detection high-pressure liquid chromatography (HPLC) 41, 42.

**Duodenal biopsy specimen**

Tissue samples from the horizontal part of the duodenum will be obtained by standard flexible gastroduodenoscope at the endoscopy unit of Maastricht University Medical Center (MUMC) and will be performed by an experienced gastroenterologist. The procedure is widely used in medical practice. Its application in human intervention trials was approved previously by this Medical Ethical Committee (MEC 01-149, MEC 03-196, MEC 05-118). Briefly, in the seated position, an anaesthetizing spray (Xylocaine 2%, Astra Pharmaceutica BV, Zoetermeer, The Netherlands) will be sprayed in the throat to locally anaesthetize the pharynx. A plastic ringlet will be placed in the mouth. The gastroscope will be inserted through the mouth, the oesophagus and the stomach, and into the proximal duodenum, respectively. Eight biopsies of approximately 5 mg of the epithelial tissue will be taken using small (standard) forceps. Upon obtaining the biopsies, the gastroscope will be retracted. The air in the stomach will be aspirated before removing the endoscope. The intestinal mucosa heals quickly from such biopsies.

The biopsy specimens will be used to determine the following:

- Mucosal ethanol and acetaldehyde concentrations.
- Tight junction functionality by
  - Transmission electron microscopy to study the morphological changes of TJs in response to ethanol.
  - Immunofluorescent labelling of perijunctional actin, myosin, ZO-1, myosin light chain kinase, and phosphorylated myosin light chain.
  - *Ex vivo* determination of the effects of ethanol and acetaldehyde on tight junction functionality using Ussing chambers.
- Expression of different genes involved in the regulation of the TJs proteins, ethanol metabolism and the inflammatory cytokines.

**Measurements in the urine**

The following parameters will be measured in urine samples, using standard laboratory protocols:

- Lactulose
- L-rhamnose
- Claudin 3
- I-FABP

**Measurement of alcohol concentration in the exhaled breath**

Blood alcohol concentration will be measured in exhaled breath by the end of each experiment. Alcohol breath testing is an indirect test, but widely used to estimate blood alcohol concentration because of the assumption that an end-exhaled breath sample accurately reflects the alveolar (or deep-lung) air which is in equilibrium with the blood.

**Safety aspects**

**Serious adverse events (SAEs)**

All adverse events reported spontaneously by the subject or observed by the investiga­tor related to ethanol infusion or intraduodenal intubation will be recorded and reported to MEC. The subjects will be closely monitored for ethanol intoxication and therapeutic interventions will be performed accordingly whenever is needed.

The subjects also might get hypoglycemic, therefore, blood glucose levels will be checked hourly. If blood glucose level is < 2.5 mmol/L, intervention with intravenous glucose will be performed.

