**Risks associated with participation:**

The possible risks in the study are related to the effects of ethanol on the nervous system such nausea, vomiting and euphoria. There are also possible risks related to the intervention with the gastroduodenoscope e.g. the risks of bleeding at the site of the biopsy and perforation of the viscera.

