The aim of the present study is to investigate the effects of “moderate ethanol drinking” (2 drinks per day, equivalent to 20 g of ethanol) on the intestinal permeability and the tight junction complex. For that aim, blood and tissue samples from the proximal small intestine will be collected. A multi-sugar test will be applied to measure the intestinal permeability in healthy individuals.

The dose of ethanol will be based on an explorative study to assess the tolerability and the minimal effective dose to induce intestinal permeability changes as well as the correct timing for biopsy. Ethanol will be administered intraduodenally to overcome interindividual differences of oral, esophageal and gastric ADH activity and to avoid the possible dilution of ethanol by gastric secretions.

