**Aims of the explorative study:**

The aims of the explorative study are:

- To establish the minimal effective dose of ethanol required to induce increased intestinal permeability.
- To assess the safety and tolerability of the dose.
- To determine the peak of blood ethanol concentration.

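### Tolerability helps set the ethanol dose, but the protocol asks no one about symptoms, so subjective intolerance may be under-recorded in the five explorative subjects

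*Protocol*

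**What the plan says.** **Role of tolerability.** The Protocol's Aims of the explorative study include: "To assess the safety and tolerability of the dose". The closing paragraphs of the Introduction tie this to the dose: "The dose of ethanol will be based on an explorative study to assess the tolerability and the minimal effective dose". For the definitive study, General considerations says of the dose: "Will be based on the results from the explorative study".

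**Size and escalation.** Under The explorative study: "Five male healthy volunteers will be included in the explorative study". The starting dose is 20 g, and "The dose will be increased gradually (i.e 30 g maximum) if necessary". The section does not say how tolerability enters that decision.

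**Expected effects.** The Abstract's section on risks names "effects of ethanol on the nervous system such nausea, vomiting and euphoria", and also bleeding at the biopsy site and perforation from the endoscopy.

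**Collection of adverse events.** Under Safety aspects, Serious adverse events (SAEs), the rule begins "All adverse events reported spontaneously by the subject or observed by the" investigator and ends "related to ethanol infusion or intraduodenal intubation will be recorded and reported to MEC". The same section provides close monitoring for intoxication and hourly glucose checks. Other sections provide a breath alcohol test at the end of each experiment and a supervised stay. The protocol gives no symptom list, grading, scheduled question or definition of a tolerated dose.

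**The concern.** A tolerability aim needs a measurement. The one collection method that the protocol states waits for the subject to speak or for the investigator to notice. Vomiting can be seen. Nausea and euphoria are largely subjective, and a man who has just received 20 g or more of ethanol in 15 minutes may not mention them. Staff meet each subject at seven scheduled blood draws, yet nobody is told to ask.

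The rule also requires a judgement of cause before an event is recorded. Read literally, it leaves out events due to the gastroscopy and biopsies, although the Abstract lists these among the risks.

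What is at stake is the quality of one input to the dose decision. Five men give little information, and incomplete capture reduces it further, in the direction that makes a dose look better tolerated than it is.

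**Working it through.** **The plan's own figure.** The protocol gives no calculation for the five explorative subjects, so there is nothing to reproduce on this point. The calculated sample size of 12 belongs to the permeability outcome of the definitive study and plays no part here.

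**Inputs.**
- n = 5, from The explorative study.
- p, the true proportion of men with a given symptom at a dose. The protocol does not give it; assumed 10% to 50%.
- c, the share of affected men whose symptom reaches the record by either route, volunteered or observed. The protocol does not give it; 1 (full capture) and 0.5 (half) are assumed.

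**Formula.** With independent subjects, P(no recorded event in 5) = (1 − p·c)^5.

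| Assumed p | Full capture, c = 1 | Half captured, c = 0.5 |
|---|---|---|
| 10% | 0.90^5 = 0.590 | 0.95^5 = 0.774 |
| 20% | 0.80^5 = 0.328 | 0.90^5 = 0.590 |
| 30% | 0.70^5 = 0.168 | 0.85^5 = 0.444 |
| 40% | 0.60^5 = 0.078 | 0.80^5 = 0.328 |
| 50% | 0.50^5 = 0.031 | 0.75^5 = 0.237 |

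**Separating the two causes.** At p = 20%, five men show no event with probability 0.328 even when everyone is asked; half capture adds 0.590 − 0.328 = 0.262. At p = 40%, the sample size alone accounts for 0.078 and half capture adds 0.328 − 0.078 = 0.250. For moderate rates, then, much of the risk is the sample size. For frequent symptoms most of it comes from capture, if capture is as poor as assumed.

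**What a clean result would show.** With 0 of 5 and full capture, the one-sided 95% upper limit for p is 1 − 0.05^(1/5) = 0.451, or 45%. With half captured, that limit applies to the recorded rate p·c, so the limit for p itself is 0.451 / 0.5 = 0.90, or 90%.

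**What the other safeguards measure.** Hourly glucose detects hypoglycaemia. The breath test estimates blood alcohol at the end of the day. Monitoring for intoxication has no stated instrument, schedule or recorded result. Supervision allows overt effects to be seen. None of these yields a graded record of nausea or discomfort.

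**Existing contact points.** Blood is drawn at −15, 15, 30, 45, 60, 120 and 180 minutes. Two details affect any schedule of questions. In the definitive study the gastroscopy is provisionally at 60 minutes, with throat anaesthesia and a mouthpiece, so it coincides with a draw. Urine collection runs for 5 hours, so about two hours follow the last draw.

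**The case against.** **Collection is not purely passive.** The sentences right after the quoted rule provide close monitoring for intoxication and hourly glucose, and subjects are supervised until a breath test clears them. This stands. Vomiting or clear intoxication would probably be seen, which narrows the gap to symptoms that are neither voiced nor visible.

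**A reader might infer that an intolerable dose could easily pass as clean.** The documents do not support that. They give neither a symptom rate nor a capture rate, and they do not define intolerance as any nausea. Low values of c also give little credit to investigator observation. A symptom too mild to mention is weak evidence that a dose is intolerable. Much of the chance of seeing no event comes from having five subjects. The range is also bounded, from the 20 g start to the 30 g maximum.

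**A reader might infer that the ethanol–placebo safety comparison in the crossover is biased by expectation.** The protocol does concede, under Alcohol administration, that participants and the investigator will notice the effects of ethanol. But no adverse-event comparison between the two days is among the stated outcomes, so no planned analysis is damaged. Scheduled questions would not remove expectation effects either.

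**The link to the dose decision is partly inferred.** The collection rule is written as a safety-reporting rule, and nothing says tolerability will be judged by counting those reports. That is true, but no other tolerability measure is stated. A checklist might exist in case report forms that are not shown. The protocol still states a method, and it does not include one.

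**Conclusion.** The point holds in a limited form. Tolerability is an aim and helps set the dose, but the only stated collection method is spontaneous report or investigator observation, restricted to events judged related to the infusion or intubation. Overt intolerance would probably be noticed; subjective intolerance may be under-recorded.

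The size cannot be fixed from the documents. If half of affected men are captured, the chance of no recorded event in five rises from 8% to 33% at an assumed 40% rate, and from 33% to 59% at an assumed 20% rate. Both rates and the capture share are assumptions. Better collection would not cure the small sample: even complete questioning with 0 of 5 leaves an upper limit of 45%.

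This does not touch the primary permeability outcome and is not a contradiction in the text. It is a weak choice of method for a stated aim, and cheap to improve.

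**What to change.** In Safety aspects, Serious adverse events (SAEs):

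1. Add a short fixed list of symptoms, each graded: nausea, vomiting, euphoria or intoxication, and abdominal pain. Ask it in identical wording on every study day (explorative, ethanol and placebo).
2. Ask it at the existing blood-sampling times, moving the question to just before the gastroscopy where a draw coincides with it, and once more at the end of the 5-hour urine collection.
3. Keep spontaneous and observed events, and record all events whatever their judged cause, including those after gastroscopy and biopsy. Relatedness can be assessed as a separate item.
4. Name the explorative-study symptom table as the tolerability result that the Introduction and the Aims of the explorative study refer to.

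**Cost.** A one-page checklist, almost entirely at contacts that already exist, with no extra visit, staff or procedure. More mild events will be on record. Expectation effects remain, because the ethanol and placebo days can be told apart. The change proposes no dose and no clinical rule.

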**Gastroduodenoscopy**

The gastroduodenoscopy, performed by a gastroenterologist, is a standard procedure that takes 10 to 20 minutes. During the procedure 8 biopsies will be taken with a standard biopsy forceps. Diagnostic upper GI endoscopy is a remarkably safe procedure. Although there are no recent high quality prospective studies of complications following diagnostic upper GI endoscopy, one large US study estimated an overall complication rate (including mucosal biopsy) of 0.13% and an associated mortality of 0.004% 44. Perforation related to diagnostic upper GI endoscopy is uncommon with an estimated frequency of 0.03 and mortality of 0.001% 44.

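### The adverse-event recording rule is limited to two causes and, read literally, leaves out gastroscopy and biopsy events that the protocol names as risks

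*Protocol*

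**What the plan says.** Safety aspects, Serious adverse events (SAEs), sets the capture rule. Events volunteered by the subject or seen by the investigator that are "related to ethanol infusion or intraduodenal intubation will be recorded and reported to MEC". The section title refers to serious events, but the sentence is worded for adverse events in general. No other sentence in the protocol says which events are to be recorded.

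The abstract, under Risks associated with participation, gives two sources of risk: the effects of ethanol on the nervous system, and "risks related to the intervention with the gastroduodenoscope e.g. the risks of bleeding at the site of the biopsy and perforation of the viscera". The Gastroduodenoscopy section under Safety aspects discusses complications, perforation and mortality for the same procedure and states: "During the procedure 8 biopsies will be taken with a standard biopsy forceps".

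Three other sections bear on safety reporting and set no limit by cause:

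- Annual safety report promises the committee a complete safety analysis.
- Follow-up of adverse events covers all adverse events until they resolve or stabilise.
- Report progress and end of study includes serious adverse events and reactions, and other problems, in a yearly summary.

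**The concern.** The rule admits an event only if it is attributed to the infusion or to the tube. The endoscopic procedure, for which the protocol itself warns of bleeding and perforation, is not on the list. An investigator who follows the sentence as written has no instruction to record a minor biopsy bleed, or throat or abdominal complaints attributed to the endoscope.

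The rule also makes the causal judgement a condition of recording. The Alcohol administration section under Methods accepts that participants and the investigator will notice the effects of ethanol. Whether a complaint enters the record can therefore depend on a judgement made by someone who may know which day it is.

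At stake is complete safety capture in healthy volunteers who undergo an invasive procedure on each of two days. The permeability outcome is not affected.

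**Working it through.** The protocol gives no figure to reproduce on this point. The check is mainly a comparison of sections, followed by a short count.

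**Step 1: does intubation include the gastroscopy?** The text with Figure 4 has subjects arrive for "blood sampling and insertion of the intraduodenal tube", before the infusion. It then schedules a different procedure: "Gastroscopy for biopsy sampling will be performed at t= 60 min", a time that may be changed after the explorative study. The section Duodenal biopsy specimen describes that procedure with its own instrument and operator: "Eight biopsies of approximately 5 mg of the epithelial tissue will be taken using small (standard) forceps". The protocol uses one term for the tube and another for the endoscope, so the natural reading of intraduodenal intubation is the tube alone.

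**Step 2: named risks against recorded causes.**

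| Source of risk | Named as a risk in the abstract | In the recording rule |
|---|---|---|
| Ethanol | yes | yes |
| Intraduodenal tube | no | yes |
| Gastroscopy with biopsy | yes | no |

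One of the two sources that the abstract names is missing from the rule, while a source that it does not name is included. This looks more like a drafting slip than a deliberate exclusion.

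**Step 3: do the other sections close the gap?**

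- Follow-up of adverse events and Annual safety report are broad, but neither says what is to be recorded in the first place. They show that the protocol intends wider capture than its rule delivers.
- Report progress and end of study does reach serious events of any cause, once a year.
- What remains uncovered is non-serious procedure events, and any reporting other than in the annual summary.

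**Step 4: how many procedures are concerned?** Inputs: 12 subjects (Samples size), two study days (The definitive study), eight biopsies per gastroscopy (Gastroduodenoscopy).

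- Gastroscopies: 12 × 2 = 24.
- Biopsies: 24 × 8 = 192.

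The explorative study as described has no gastroscopy, so it adds none.

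**Step 5: how many complications would be expected?** The Gastroduodenoscopy section cites an overall complication rate, including mucosal biopsy, of 0.13%.

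- Expected number: 24 × 0.0013 = 0.031.
- Chance of at least one: 1 − (1 − 0.0013)^24 = 0.031, about 3%.

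This treats procedures as independent. The cited rate may not count minor complaints, which are the events the gap mainly affects, and the protocol gives no rate for those.

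**The case against.** The strongest case on the other side has four parts.

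1. *The broader sections already cover the matter.* An event cannot be followed to resolution, or enter a complete safety analysis, without being noted, and a perforation or significant bleed would normally count as serious. This stands for serious events. A reader might infer that serious biopsy complications would go unreported, or that the annual safety report would be incomplete. The documents do not support that, because the annual provisions carry no filter by cause. For non-serious events the objection shows only that the sections disagree.

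2. *No planned comparison is harmed.* A reader might infer that a planned ethanol-versus-placebo safety comparison is biased by selective recording. The documents do not support that either. Safety and tolerability is an aim of the explorative study only, which as described has no placebo day. The outcomes of the definitive study include no comparison of adverse events between periods, and Data analyses describes none. Nor is there any evidence that a given complaint would be recorded less often on the placebo day. The tube is placed on both days, so tube-related complaints qualify on both. Unequal capture is a possibility and supports the point only in second place.

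3. *The sentence can be read another way.* The qualifier may apply only to events seen by the investigator, so that anything the subject volunteers is recorded. The grammar allows this. Even so, gastroscopy events seen by the investigator remain outside.

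4. *The expected count is very small.* This is correct at the cited rate, as step 5 shows. The numbers 24 and 192 count procedures and biopsies, not lost events. The point rests on a faulty rule, not on a high expected number of complications.

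**Conclusion.** The point holds in a limited form. Read literally, the recording rule omits events from the gastroscopy and biopsies of the definitive study, contrary to the protocol's own list of risks, and it is narrower than three other safety sections. Its scope is 24 planned gastroscopies. The practical gap is mainly non-serious procedure events and reporting outside the annual summary.

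This rests on three assumptions: that all 12 subjects complete both days, that intraduodenal intubation means the tube, and that a serious bleed or perforation would be listed in the annual progress summary. An investigator might well record a biopsy bleed anyway, but the written rule does not ask for it.

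**What to change.** Reconcile the rule under Serious adverse events (SAEs) with Risks associated with participation, Gastroduodenoscopy, Annual safety report, Follow-up of adverse events, and Report progress and end of study. The simplest way is to delete the qualifier by cause, so that every adverse event on both study days is recorded whatever its presumed cause. Relatedness then becomes a separate field on the form, with the categories ethanol, tube, gastroscopy or biopsy, and other.

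Adding gastroscopy and biopsy to the list of causes would close the textual gap too. It would still leave recording dependent on a causal judgement by someone who may recognise the ethanol day, so removing the qualifier is better.

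The cost is one sentence, one form field and a few more minor events to log. The design, sample size and analysis do not change.
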